#### Sample Size

Based on pilot data involving 10 participants with a first episode of psychosis, the mean baseline score was 6.5 (SD 1.3). The effect size is 1.17 (18% × 6.5) to detect a difference of 18%. The standardized effect size (E/S) is 0.9 (1.17/1.3 [effect size/SD]). The power calculations [64] suggest that 20 participants are sufficient per group. With a minimum of 24 participants per gender and racialized group at visit 1, there would be at least 20 participants per group by visit 3 (up to 4 weeks later), with a projected dropout rate of 15%.

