### Visit 1: Baseline Assessments

#### Study Population

The eligibility criteria are as follows: (1) meet the criteria for a first episode of psychosis defined as the first illness episode involving psychosis symptoms; (2) meet DSM-5 (Diagnostic and Statistical Manual of Mental Disorders, 5th Edition) criteria for a psychotic disorder and a lifetime or current cannabis use disorder (up to 45% of people with a first episode of psychosis will meet the criteria for cannabis use disorder [16,47,48]; patients diagnosed with cannabis-induced psychosis by definition meet the criteria for both conditions [49] and will be eligible); (3) be between the ages of 16 and 30 years; (4) self-identify as a Black African or Black Caribbean first- or second-generation immigrant (English speaking), or belong to any ethnic group; (5) be a client of an early psychosis intervention with up to 12 months of service; and (6) be fluent in English.

Participants will self-identify and be divided into the following disaggregated ethnic and racialized groups: Black African (n=24), Black Caribbean (n=24), and any ethnicity (n=24). There may be significant differences in social and community norms for cannabis use between Black African and Caribbean groups and differences in English proficiency, educational attainment, and immigrant status. Sex will be defined based on sex assignment at birth. Gender will be self-assigned as man, woman, transgender, fluid, two-spirit, and non-binary. Equal numbers of men (including transmen) and women (including transwomen) will be enrolled for each racialized group. Participants will self-identify as nonimmigrant, or first- or second-generation immigrant.

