#### Hypothesis

We hypothesize a significantly greater knowledge test score (>18%) in the group first exposed to the Back to Reality Series compared to the control game. We expect this finding for Black African and Black Caribbean groups, Black men, Black women, and all ethnic groups with a first episode of psychosis and cannabis use disorder.

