#### Data Collection and Procedures

The video games will be streamed over Zoom by the research staff. Participants will be randomized to determine the gameplay order (either the Back to Reality Series or the control game will be played first). A software program embedded within the download of the Back to Reality Series randomly assigns the order in which each participant plays the first game on a 1:1 basis. The randomization is not to allocate participants into groups. The experimental and control games are packaged on the screen to protect the blinding at the outset. However, the video games are not associated with preconceived notions of therapeutic benefit, which minimizes bias. The video games are password protected, so participants will not have had prior access.

Subsequently, participants will complete a quiz measuring factual knowledge about the impact of cannabis on psychosis. Participants are randomized so that differences in quiz scores can be attributed to gameplay interventions, which is an advantage over pre-post gameplay designs for quantitative analysis. This process also avoids having participants complete the same or similar quiz twice in a day. The research staff will conduct the knowledge test by displaying the questions to the participants and reading out each item. After completing the quiz, participants will immediately play whichever game remains. Thus, if the participant was randomized to play the Back to Reality Series first, the control game, Morpheus’ Spell, will subsequently be played.** **Each participant will complete a gameplay survey about the Back to Reality Series. Finally, participants will undergo a second qualitative interview to discuss ideas and impressions from their gameplay experiences and reflect upon their views about the relationship between cannabis and psychosis after playing the game.

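### The sample size of 20 is a per-arm requirement, but the protocol counts it as met by whole racialized and gender groups that are then split 1:1 by game order, leaving about 10 per arm in each named subgroup

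*Protocol article*

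**What the plan says.** The Sample Size section under Visit 3 starts from pilot data on 10 people with a first episode of psychosis, in whom "the mean baseline score was 6.5 (SD 1.3"). It takes 18% of 6.5, or 1.17 points, as the target difference and divides by the SD: "The standardized effect size (E/S) is 0.9 (1.17/1.3 [effect size/SD"]). From this it concludes that 20 per group is enough, and it regards that number as secured: "With a minimum of 24 participants per gender and racialized group at visit 1, there would be at least 20 participants per group". The retained number refers to Visit 3, after an allowance of 15% for dropout. Alpha, sidedness and target power are not given.

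The Study Population section sets enrolment at "Black African (n=24), Black Caribbean (n=24), and any ethnicity (n=24"), 72 in all, and adds: "Equal numbers of men (including transmen) and women (including transwomen) will be enrolled for each racialized group".

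The Hypothesis section predicts a higher score in those first exposed to the Back to Reality Series than in those first exposed to the control game. It extends the prediction to subgroups: "We expect this finding for Black African and Black Caribbean groups, Black men, Black women, and all ethnic groups". The Visit 3 Quantitative Analysis section names the t test.

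Data Collection and Procedures under Visit 3 randomises game order 1:1 and places the single quiz between the first and second game. The same section says: "The randomization is not to allocate participants into groups".

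**The concern.** The word *group* carries two meanings in the Sample Size section. In the power calculation it is one side of a two-sample comparison. In the next sentence it is a racialized or gender category. These are not the same unit, because every category contains participants from both game orders.

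Each participant takes the quiz once, so there is no within-person contrast to recover precision. The comparison inside any category is between its Back-to-Reality-first members and its control-first members, each about half of the category. The statement that randomisation does not form groups obscures this, because the Hypothesis and the t test compare exactly the two sets that randomisation creates.

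At stake is a stated claim of adequacy for the communities the study is chiefly about. A reader of the protocol would take a non-significant result among, say, Black Caribbean participants to come from a comparison with about 80% power, when it would have about half.

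**Working it through.** **Inputs.** From the Visit 3 Sample Size section: difference 1.17, SD 1.3, 20 per group, 24 enrolled, 15% dropout. From Study Population: 24 in each of three racialized groups, with equal men and women. From Data Collection and Procedures: 1:1 game order, one quiz per participant. From the section describing the games: arm SDs of 1.6 and 1.9 in the randomised pilot of 55 youth experiencing homelessness. Assumed, because not stated: two-sided alpha 0.05 and 80% power.

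**1. Reproduce the plan's figure.**
- Target difference: 0.18 × 6.5 = 1.17. Standardised: 1.17 / 1.3 = 0.90.
- Normal approximation: n per arm = 2 × (1.960 + 0.842)² / 0.90² = 19.4, rounded up to 20.
- Noncentral t: 20.4 per arm.
- Dropout: 20 / 0.85 = 23.5, rounded up to 24; and 24 × 0.85 = 20.4.

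So 20 reproduces as the number in each arm, and 24 as that number inflated for dropout.

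**2. Find the arm size inside each named subgroup.**
- Black African: 24 enrolled, 20.4 retained, 20.4 / 2 = about 10 per arm. Black Caribbean: the same.
- Black men: 12 + 12 = 24 across the two Black groups, if nearly all participants are men or women; again about 10 per arm. Black women: the same.

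**3. Power for 1.17 points at about 10 per arm.**

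| Assumption | Power |
|---|---|
| SD 1.3, two-sided 0.05, t test | 48% |
| SD 1.3, two-sided 0.05, normal approximation | 52% |
| SD 1.3, one-sided 0.05, t test | 61% |
| SD 1.3, two-sided, t test, no dropout (12 per arm) | 56% |
| SD 1.6, two-sided, t test | 34% |
| SD 1.9, two-sided, t test | 26% |

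At 20 per arm and SD 1.3 the two-sided figures are 79% (t test) and 81% (normal approximation).

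**4. What 10 per arm can detect (SD 1.3, two-sided).**
- With 80% power: 1.325 × 1.3 = 1.72 points; 1.72 / 6.5 = 26%.
- Smallest observed difference reaching P<.05: 2.101 × 1.3 × √(2/10) = 1.22 points. An observed 1.17 (18%) would fall just short.

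**5. Pooled comparisons (t test, two-sided 0.05).**

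| Comparison | Retained | Per arm | SD 1.3 | SD 1.6 | SD 1.9 |
|---|---|---|---|---|---|
| Both Black groups | 48 × 0.85 = 40.8 | about 20 | 79% | 62% | 48% |
| All participants | 72 × 0.85 = 61.2 | about 30 | 93% | 80% | 65% |

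**6. What the subgroup claim would need.** 20 per arm within a subgroup is 40 completers; 40 / 0.85 = 47.1, so 48 enrolled, against 24 planned.

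**The case against.** Several objections have force.

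- **No alpha, sidedness or power is stated.** A reader might infer that power is under one half, so that a game working as assumed would fail in each subgroup more often than not. The documents do not support so firm a line. The t test gives 48%, but the normal approximation, which itself yields the stated 20, gives 52%, and a one-sided test gives 61%. The gap from about 80% is secure; the side of 50% is not.
- **The subgroup sizes are not all fixed.** The Sample Size section calls 24 a minimum, so 12 per arm at entry is the planned figure and not a ceiling. The 24 for Black men and for Black women is inferred from the equal split, and Study Population also lists other gender categories.
- **The phrase on gender and racialized groups could be read as 24 per gender-by-race cell.** Six such cells would need 6 × 24 = 144 participants. Study Population rules this reading out: 24 per racialized group, half men and half women, is 12 per cell. No charge of a missing 72 participants follows.
- **The study is framed as feasibility work with qualitative primary questions at Visit 2.** That limits the damage, and the full-sample comparison is adequately powered at SD 1.3. It does not excuse the claim, because the protocol states a directional hypothesis for each subgroup and says the numbers suffice.
- **Misreading of a null subgroup result is a risk, not a plan.** No section says that a non-significant subgroup result will be taken as no benefit.

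None of these makes a group of 24 supply 20 per arm.

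**Conclusion.** The stated calculation is applied to the wrong unit. The 20 is a per-arm requirement, and each racialized or gender subgroup in the Hypothesis section has about half of it. For Black African and Black Caribbean participants this follows directly from the enrolment figures. For Black men and Black women it holds if nearly all participants are men or women.

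Under the protocol's own difference and SD, two-sided power in each is about 48% to 52%, against roughly 80% implied. If the SD is nearer the 1.6 to 1.9 seen in the randomised pilot, which was in a different population, t-test power is 34% to 26%. These figures assume alpha 0.05 and an even split by game order.

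A reader might infer that the whole quiz comparison is underpowered. On the stated SD it is not: all 72 give about 30 per arm and 93%, taking the reference to all ethnic groups in the Hypothesis section to mean the full sample. The pooled figures depend on an SD from 10 people and fall to 80% to 65% at SD 1.6 to 1.9. Nor do the documents say which comparison is primary. The combined Black groups and the full sample are both defensible, and that choice belongs to the investigators.

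**What to change.** In the Visit 3 Sample Size section:

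1. State the requirement as 20 per randomised arm, with the alpha, sidedness and power assumed.
2. Withdraw the claim that each gender or racialized group is large enough. Give its size as about 10 per arm at Visit 3, with two-sided power of about 48% to 52% for 1.17 points at SD 1.3, and say that these subgroups will be reported as estimated differences with confidence intervals.
3. State that only pooled comparisons reach 20 or more per arm: both Black groups combined (about 20 per arm, 79%) and all participants (about 30 per arm, 93%). Show power at SD 1.6 to 1.9 alongside (62% to 48%, and 80% to 65%). The investigators should name which comparison is primary.

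Bring the Hypothesis section into line, so that subgroup expectations are not presented as separately powered tests. In Data Collection and Procedures, reword the sentence saying that randomisation does not form groups: it forms the two game orders that the t test compares, and each participant plays the other game after the quiz.

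The cost is wording only. No extra participants are needed. The stated subgroup power becomes less favourable.

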## Results

We began recruiting participants for this study in September 2021. So far, we have had 2 advisory committee meetings, one in October 2021 and the second in December 2021. Recruitment is being tailored to fit with the pandemic-related restrictions. The recruitment target is expected to be met by December 2022. Full analysis of the results will be completed subsequently.

## Discussion

The anticipated findings for this study center around knowledge exchange about cannabis and psychosis, and engaging young people experiencing a first episode and, in particular, those of Black African and Caribbean descent. We expect the video games to encourage meaningful discussions about cannabis and psychosis. We hope the characters, narrative, interactivity, and video gameplay promote retention and engagement. The PCT Quiz will verify knowledge acquisition. Attitudes and satisfaction will be documented by qualitatively analyzing themes reviewed by the advisory council. The Back to Reality Series, combined with tutorials led by university students, has been shown in a pilot study involving healthy participants to be enjoyable and to transfer knowledge about cannabis and psychosis to youth from Black communities [42].

The strength of this protocol includes community engagement provided by the advisory council, which promotes research priorities and interpretations that are more acceptable to youth with serious mental illness and young people from Black communities. A limitation of the design includes the lack of follow-up to document the long-term impact of the games.

Few Canadian studies report cannabis use based on race or ethnic groups; nevertheless, ethnic differences have been found between young people of Black African background and those of Black Caribbean background, with the latter group more likely to report problematic use [23]. Studies conducted in the United States involving healthy populations have shown that Black youth are more likely than White youth to report self-medicating with cannabis to relieve physiological symptoms associated with anxiety [65]. However, many studies suggest that youth use cannabis because they believe it will alleviate anxiety symptoms regardless of race, but no studies to date indicate that youth self-medicate to ease psychosis symptoms [66,67]. This study is unique because it will explore the intersections of race, ethnicity, and cannabis use among young people experiencing their first episode of psychosis.

Future directions include using digital video games as psychoeducational products that explore credible scientific knowledge about the risks and benefits of cannabis use. The video games provide a unique opportunity to reach young people from Black communities with the help of community partners. The Back to Reality Series could offer a coherent knowledge transfer strategy for education and engagement. Moreover, the Back to Reality Series could become a sustainable evidence-based online knowledge translation product, reaching an appropriate audience through networks connected to early interventions in psychosis and community agencies. Validation of the psychoeducational value of the Back to Reality Series could support future studies examining its ability to promote readiness for change and its ability to improve not only insight but also engagement with cannabis use disorder treatments offered by early intervention programs.

## Appendix

Multimedia Appendix 1 CIHR peer review.

## Abbreviations

CBT: cognitive behavioral therapy
DART: Diagnostic Assessment Research Tool
DAST: Drug Abuse Screening Tool
DSM-5: Diagnostic and Statistical Manual of Mental Disorders, 5th Edition
PCT: Psychosis and Cannabis Test
THC: delta-9-tetrahydrocannabinol
